**Table 1 Tab1:** **Grading system for catheter tip location**
[21] **with additional grades 1a/1b**

Grade	Accuracy of placement	Location of catheter tip
1	Optimal/adequate	Ipsilateral frontal horn, including tip of third ventricle: 1a, no contact with ventricle wall; 1b, contact with ventricle wall
2	Suboptimal in non-eloquent tissue	Contralateral frontal horn or lateral ventricle/corpus callosum/interhemispheric fissure
3	Suboptimal in eloquent tissue	Brainstem/cerebellum/internal capsule/basal ganglia/thalamus/occipital cortex/basal cisterns

#### Secondary outcome measures

The secondary outcome measures will be the frequency of placements required, the frequency of completed placements within the ventricle of the perforated part of the catheter tip, the frequency of very early and early shunt failures (revision of the ventricular drainage within 24 hours and within the hospital stay), and the frequency and percentage of complications (procedure-related and nonsurgical) at discharge. The effect size will be measured using relative risk, absolute risk reduction, and numbers needed to treat where possible.

### Data documentation

The following parameters will be recorded and used to demonstrate successful randomization and the presence of even baseline groups (Table 
1):Age (years);Gender (nominal male/female);Glasgow Coma Score on admission (ordinal, 1 to 15-point scale);Cause of hydrocephalus/slit ventricles Preoperative ventricle size - width (millimeters);Preoperative ventricle size - using the frontal occipital horn ratio (FOHR; millimeters);Preoperative ventricle size - and the width of the lateral ventricle in the coronal plane between the medial wall of the corpus callosum and the septum;Preoperative ventricle size - using the Evans ratio (bifrontal ventricular span, the ratio of maximum width of the frontal horns to the maximum width of the inner table of the cranium; millimeters),Episode of care (nominal, *de novo*/revision) Time from symptom onset to *admissi*on (hours);Time from symptom onset to randomization (hours);Time from symptom onset to EVD (external ventricular drainage placement (hours);Duration of hospital stay (days);Duration of EVD being in place (days);Presence of CSF infection during the first 14 days, as defined by modified clinical diagnostic criteria for device-associated meningitis (treatment required on either positive culture, or elevated cell count, red cell:white cell ratio, increased lactate, and/or decreased glucose (nominal, yes/no) [22].The EVD catheter placed for ventriculoperitoneal shunting (nominal, yes/no).Any associated endoscopic procedure, for example, third ventriculostomy (freetext);Neurosurgical experience of primary operator (years).

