### Outcome assessment

#### Primary outcome measures

The first primary outcome measure will be the frequency and percentage of correct placements of the ventricular catheter, assessed by the three-point scale of Kakarla *et al*., with an additional 1a/1b criteria (Table 
1)
[21]. The effect size will be measured using relative risk, absolute risk reduction, and numbers needed to treat. The second primary outcome measure will be the frequency and percentage of acute ventricular revisions (within one week for an improperly placed catheter). Assessment is performed by an investigator blinded to the study allocation. The effect size will be measured using relative risk, absolute risk reduction, and numbers needed to treat.

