### Adverse events and severe adverse events

The term adverse event (AE) describes any sign, symptom, syndrome, or any disease occurring newly in a trial participant after consent to the trial and being of particular interest for the assessment of the disease or the security of the therapeutic concept. Any AE is documented in the CRF or electronic file of the patient.

For the purposes of this trial the definition of an adverse event will consist of any one of the following:Impairment of the general condition of the patient,Physical injury, including falls,Infection other than wound infection, sepsis or Systemic Inflammatory Response Syndrome (SIRS) Intracranial bleeding in the proximity of the ventricular catheter,Wound infection or dehiscence at the emersion site of the ventricular catheter,Newly occurred neurological deficit,Arterial or venous thrombosis,Any suspicious findings that may have relationship to the study.

For the purposes of this study the definition of a serious adverse event (SAE) will consist of any one of the following:Fatal events or death,Any life-threatening condition,Disabling or incapacitating events,Events that require prolongation of hospitalization,Events that require intervention to prevent permanent impairment.

The relation of the AE or SAE (as a cause or result) to any other AE or SAE will be scored on a two-point scale; 0 - no, 1 - possible (brief description), or 2 - yes (give brief description). The investigator’s estimation of the severity of the problem to the study or study device (to be measured only, if the AE or SAE is or might be related to study) will be measured and scored on a three-point scale; 1 - mild, 2 - severe, or 3 – life-threatening. The investigator’s recommendation to change the protocol, informed consent, or assent form will be given as a binary answer of yes (with a brief description) or no. The outcome of AE or SAE will be assessed until discharge using a four-point scale; 1 - full recovery, 2 - permanent deficit, 3 - not yet fully recovered, or 4 - not known.

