### Reporting and statistical analysis

The reporting of this trial will conform to the reporting guidelines outlined in the Consolidated Standards of Reporting Trials (CONSORT) for non-pharmacological interventions statement of 2010
[25]. The statistical analysis will be by the intention-to-treat principle. The occurrence of the primary outcome (number and frequency of correct ventriculostomy) will be compared between the two randomization groups. The secondary outcome analyses will compare the above-described variables between randomization groups. Subgroup analyses will be performed to evaluate whether other parameters such as age, ventricle size, diagnosis, or experience of the surgeon may influence the results. Data are presented as mean and standard deviation or as median with 25/75 percentiles. Stata version 11.2 StataCorp. 2013. *Stata Statistical Software*, College Station, Texas, United States) will be used for all analyses.

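### Hospital stay, EVD duration and 14-day CSF infection are listed as evidence of even baseline groups, although all three arise after randomisation

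*Protocol article*

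**What the plan says.** Under Data documentation, the protocol article introduces one list of parameters and gives it one use: they "will be recorded and used to demonstrate successful randomization and the presence of even baseline groups". The list opens with ordinary baseline items: age, gender, Glasgow Coma Score on admission, cause, and preoperative ventricle size. It continues, under the same introduction, with "Duration of hospital stay (days);Duration of EVD being in place (days);Presence of CSF infection during the first 14 days". It also includes the time from symptom onset to EVD placement, next to the time from symptom onset to randomisation.

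The outcome sections do not name these items. Under Primary outcome measures, the first outcome is correct placement, and for the other, "The second primary outcome measure will be the frequency and percentage of acute ventricular revisions". Secondary outcome measures covers the number of placements, position of the perforated part of the catheter, very early and early failures, and "the frequency and percentage of complications (procedure-related and nonsurgical) at discharge". Reporting and statistical analysis then states that "The secondary outcome analyses will compare the above-described variables between randomization groups".

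**The concern.** A comparison of baseline groups informs about randomisation only if the items compared were fixed before allocation. For such items any difference between arms is due to chance, or to a fault in the allocation process. For items that arise later, a difference can also be an effect of the technique under test. The comparison then cannot separate the two explanations, and similar values are no evidence of sound randomisation either.

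An effect on these items is plausible on the trial's own reasoning. The guide is meant to reduce multiple passes and misplacement, and revisions are among the outcomes. Fewer passes or revisions could change infection, drainage time and stay. At stake is how a benefit or harm on these items would be labelled in the report, and whether the one carefully defined infection measure is presented as a comparison of treatments.

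**Working it through.** The protocol gives no figure on this point, so the check sets the listed items against the moment of randomisation.

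**1. When each item becomes known.** Under Randomization, allocation follows consent, and surgery follows allocation.

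| Item | Known when | Baseline? |
|---|---|---|
| Age, gender, admission Glasgow Coma Score, preoperative ventricle size | Before allocation | Yes |
| Time from symptom onset to randomisation | At allocation | Yes |
| Time from symptom onset to EVD placement | At surgery | Partly |
| Duration of EVD in place | At removal | No |
| Duration of hospital stay | At discharge | No |
| CSF infection in the first 14 days | Up to 14 days (taken to run from placement) | No |

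The infection item reads "Presence of CSF infection during the first 14 days, as defined by modified clinical diagnostic criteria for device-associated meningitis". A device-associated infection presupposes the device, so it follows the procedure being compared.

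The time to EVD placement splits as:

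onset to EVD = (onset to randomisation) + (randomisation to EVD)

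The first term is already listed separately and is a baseline item. What the longer interval adds is the second term, which lies wholly after allocation.

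**2. Where infection could otherwise be analysed.**

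- Primary outcomes: not named.
- Secondary outcomes: not named. It fits the general complications outcome, which is assessed at discharge. The abstract expects an average follow-up of two weeks, so the two windows are similar on average but differ for individual patients.
- Adverse events: the definition includes "Infection other than wound infection, sepsis or Systemic Inflammatory Response Syndrome (SIRS", which can cover CSF infection without naming it. Interim analyses has adverse events assessed at the interim look.

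Infection is therefore not lost. The measure with a 14-day window and the meningitis criteria, however, appears only in the list meant to show balance.

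**3. Illustration under assumed values.** The protocol gives no infection rates and no standard deviations, and it plans no significance test of balance. The figures below only show that a true effect could be visible as an apparent imbalance at n = 118 per arm (the figure under Sample size analysis).

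For two proportions, with p̄ their mean:

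power = Φ{[ |p1 − p2|·√n − 1.96·√(2p̄(1 − p̄)) ] / √(p1(1 − p1) + p2(1 − p2))}

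- 10% vs 5%: (0.543 − 0.730) / 0.371 = −0.504, giving 31%
- 15% vs 7.5%: (0.815 − 0.876) / 0.444 = −0.138, giving 45%
- 20% vs 10%: (1.086 − 0.990) / 0.500 = 0.193, giving 58%

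For stay or EVD duration, with a shift of d standard deviations, power = Φ(d·√(n/2) − 1.96), where √59 = 7.681:

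- d = 0.2: Φ(−0.424) = 34%
- d = 0.3: Φ(0.344) = 63%
- d = 0.4: Φ(1.112) = 87%

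With no effect, each would be 5%.

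**The case against.** The strongest reply is that this is a loosely worded introduction to a data-collection list and that nothing in the analysis depends on it. Most of that stands, and it rules out several stronger readings.

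- *A real effect would be declared failed randomisation.* A reader might infer this from the stated purpose. The article sets no balance test, no threshold and no action on imbalance, so it is a risk of interpretation and not a planned step. For the same reason, the percentages in the illustration do not describe any analysis in this trial.
- *The treatment effect would be biased by adjustment.* No covariate adjustment is planned, and the analysis is by intention to treat. The subgroup factors named (age, ventricle size, diagnosis, surgeon experience) are pre-treatment. They are given as examples, so the set is open, but nothing suggests that stay, EVD duration or infection would be added.
- *Infection is not an outcome at all.* It is not named as one, but a device-associated infection fits a procedure-related complication, and adverse events can cover it too. A condensed article need not itemise every complication.
- *Associated endoscopic procedures are also misplaced.* The article does not say when these are decided. They may follow from the diagnosis before allocation, so this item cannot be counted.

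The reply does not remove the core. The fault is a use that the article states, not a detail left to another document. For three items that use is wrong, and for a fourth it is partly wrong.

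**Conclusion.** The point holds in a limited form. Three listed items (hospital stay, EVD duration, 14-day CSF infection) are post-randomisation measures, and time to EVD placement is partly one. Their distribution across arms cannot show whether randomisation succeeded, and it may reflect the technique. The 14-day CSF infection measure is tied only to the balance check, although infection as such can still be counted under complications or adverse events.

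The primary analysis and the sample size are unaffected. The amount of any misreading cannot be derived from the article. The conclusion rests on the order consent, randomisation, surgery, and on the 14-day window starting at placement, which the device-associated definition implies but the text does not state. The correction should be made because it is specific and keeps a possible treatment effect from being presented as evidence about allocation.

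**What to change.** Split the list under Data documentation in two.

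1. Under the sentence on even baseline groups, keep only items fixed before randomisation.
2. State that CSF infection in the first 14 days, by the definition already given, is compared between arms under intention to treat as part of the secondary complications or safety outcome.
3. Report hospital stay, EVD duration and time from symptom onset to EVD placement descriptively by arm as post-randomisation measures. State that they serve neither as baseline characteristics nor as adjustment covariates. They need not become endpoints.

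The cost is a change of wording. The same data are collected, and neither the sample size nor the interim rule changes.

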### Sample size analysis

Sample size analysis estimates (hit and miss rates) were based on the results of observational studies. In a recent study of our group on the accuracy of ventricular catheter placement, using anatomic landmarks versus neuronavigation or XperCT-laser guidance, ventricles were hit in 69.2% of catheter insertions (31% miss rate) using anatomical landmarks (non-assisted), as compared to 82.3% with the use of guidance (neuronavigation or XperCT-guidance, *P* = 0.043)
[23]. The placements that were non-assisted were significantly more likely to be extraventricular than those using guidance (odds ratio: 3.73; 95% confidence interval: 1.24 to 11.19; *P* = 0.019). Given data from other retrospective studies on ventricular catheters (in the context of ventriculoperitoneal shunts), similar rates of between 25 and 45%
[4–7] malpositioning are described.

To detect a relative risk of 0.5, which is an absolute risk reduction of 15.5%, 118 patients in each of the two study arms are needed to gain a power of 80%, using a two-sided significance level of 95%. The final planned study size is to include and randomize 236 patients
[24].

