#### Randomization

The randomization process will start as soon as possible after consent to the study has been obtained. Any patient meeting the inclusion criteria and not violating the exclusion criteria may participate in the VENTRI-GUIDE study and be randomized to either a guided or freehand ventriculostomy. Online randomization will be performed by the treating physician in the study center using permuted blocks, to ensure an equal number of patients in both study arms.

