### Interim analyses

This trial will follow a group sequential design, with two stop-points (interim and final analysis; K = 2). The trial will stop if efficacy rules are met. The endpoints assessed at the first stop-point will be based on primary outcomes and adverse events. The first will be the interim analysis which will occur after the accrual of 60 patients in each arm (120 total), thus representing an information fraction of 0.51 at interim analyses. For the efficacy stop-point the commonly used O’Brien-Fleming approach will be used, and a *P* value of 0.0051 at the interim and 0.0415 at the final analysis will be used
[26].

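### The sample size section gives the two-sided significance level as 95%; the planned 118 per arm reproduces at 5%, and the article states no other overall alpha

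*Protocol article*

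**What the plan says.** The Sample size analysis section of the protocol article takes the control rate from the group's own observational study, where "ventricles were hit in 69.2% of catheter insertions (31% miss rate) using anatomical landmarks". It then sets the effect: "To detect a relative risk of 0.5, which is an absolute risk reduction of 15.5" per cent. From these it concludes that "118 patients in each of the two study arms are needed to gain a power of 80" per cent, "using a two-sided significance level of 95" per cent. The total follows as twice 118: "The final planned study size is to include and randomize 236 patients". The Randomization section fixes equal allocation, with permuted blocks used "to ensure an equal number of patients in both study arms".

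The Interim analyses section describes a group sequential design with one interim look after 60 patients per arm (120 in total, information fraction 0.51) and a final analysis. It names the O'Brien-Fleming approach and gives a P "value of 0.0051 at the interim and 0.0415 at the final analysis will be used". It does not name the overall error rate that these two thresholds are meant to preserve. The Reporting and statistical analysis section states no significance level.

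**The concern.** A significance level is the probability of rejecting a true null hypothesis. A level of 95% is not a usable value for it; 95% is the confidence level that goes with a significance level of 5%. The slip stands in the sentence that fixes the size of the trial, and it is the only place where the article gives an overall level.

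The sample size, the power statement and the split of error between the two looks all refer to the overall alpha. A reader who wants to confirm the intended value would turn to the interim thresholds. If those added up to 5%, the slip would be harmless. The check below shows that they do not quite do so, which leaves it open whether 0.0415 is deliberately cautious, is itself an error, or was set against some other overall level.

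**Working it through.** **Inputs.** From Sample size analysis: control miss rate p1 = 0.31; relative risk 0.5, so guided miss rate p2 = 0.155 and difference d = 0.155; power 80%; 118 per arm. From Randomization: 1:1 allocation. From Interim analyses: look after 120 patients; two-sided thresholds 0.0051 and 0.0415. Two-sidedness at the looks is assumed, in line with the sample size section.

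**Step 1: which level reproduces 118?** The pooled-variance formula for two proportions is

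n = [z(1−α/2)·√(2·p̄(1−p̄)) + z(power)·√(p1(1−p1) + p2(1−p2))]² / d²

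with p̄ = (0.31 + 0.155)/2 = 0.2325. The two square roots are √(2 × 0.2325 × 0.7675) = 0.5974 and √(0.2139 + 0.1310) = 0.5873.

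At α = 0.05: n = (1.960 × 0.5974 + 0.8416 × 0.5873)² / 0.155² = 1.6651² / 0.02403 = 115.4, so 116 per arm.

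Variants at α = 0.05:

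| Variant | Per arm |
|---|---|
| Common variance under both hypotheses | 117 |
| Pooled, unrounded rates 30.8% and 15.4% | 117 |
| Unpooled variance | 113 |
| Arcsine | 114 |
| Pooled with continuity correction | 128 |

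The pooled and common-variance results lie within 2% of 118.

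**Step 2: power at the planned size.** Power = Φ[(d·√118 − z(1−α/2) × 0.5974) / 0.5873]. With d·√118 = 1.6837 and α = 0.05, this is Φ[(1.6837 − 1.1709)/0.5873] = Φ(0.873) = 80.9%. The stated 80% holds at a two-sided 5% level.

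**Step 3: can 95% be meant literally?** No. A two-sided test that rejects a true null 95% of the time has at least 95% power at any sample size: with both rejection tails counted, 95.3% at 2 per arm and 99.9% at 118 per arm. No sample size gives 80% power at that level, so 118 cannot have come from it.

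**Step 4: do the interim thresholds supply the overall level?** The information fraction is 120/236 = 0.508, so the correlation between the two test statistics is √0.508 = 0.713. The critical values are 2.801 for 0.0051 and 2.038 for 0.0415. From the bivariate normal distribution,

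overall α = 1 − P(|Z1| < 2.801 and |Z2| < 2.038) = 0.0436.

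The two looks together spend about 4.4%. Holding the interim threshold at 0.0051 and solving for an overall 0.05 gives a final threshold of about 0.048.

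**Step 5: what hangs on the answer.** Fixed-sample power at 118 per arm is 80.9% at α = 0.05 and 78.6% at α = 0.0415 (same formula with z = 2.038). The second figure ignores the small contribution of the interim look. The gap is about two percentage points.

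**The case against.** The strongest reply is that this is a slip any statistician corrects on sight. The intended 5% can be recovered from the event rates, power and sample size in the same section, and the stage thresholds come to just under 5%. A condensed article may also leave the total alpha to the full protocol or analysis plan. Much of this stands: the size of the trial is sound at 5%, and nobody would analyse the data at a level of 95%. But leaving a figure to another document differs from printing a wrong one, and the wrong one is what the article prints. The thresholds also do not settle the matter, since they spend 4.4% and not 5%.

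Three stronger readings are tempting, and the document does not support them.

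- A reader might infer that the trial's type I error rate is itself wrong, or that the trial would run at a 95% false positive rate. It would not: rejection is governed by 0.0051 and 0.0415.
- A reader who puts α = 0.95 into the usual formula obtains 12 per arm and might infer that the plan is ten times too large. That figure is an artefact of a formula that counts only one rejection tail, as Step 3 shows.
- A reader might say that 118 fits 5% and nothing else. The unpooled formula at 0.0415 gives 119.1 before rounding, which is about as close. Five per cent is the natural reading, not a proven one.

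**Conclusion.** The stated significance level is wrong and should be corrected. This is an error of statement in a core design figure, not an error in the sample size: 118 per arm matches a two-sided 5% level (116 to 117 per arm; power 80.9% at 118). The decision rules as written hold the overall two-sided error at about 4.4%, so the operating error rate is below 5%, and nothing here shows it to be inflated. It would be too much to say that the plan cannot be checked, since Steps 1 and 2 check it once 5% is assumed.

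The result rests on miss rates of 31% and 15.5%, equal allocation, the normal approximation, two-sided thresholds at both looks, and the interim look falling at 120 of 236 patients. It concerns a single test at each look. The full protocol and the analysis plan were not available; if they state an overall level, the article still needs to agree with them.

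**What to change.** In Sample size analysis, replace the phrase with an overall two-sided significance level of 5%. In Interim analyses, add one sentence saying that the interim and final thresholds are set against that overall 5%, and that 0.0051 and 0.0415 at 120 of 236 patients together spend about 4.4%. The sponsor should then either say that the unspent part is intended or revise the final threshold; with 0.0051 kept at the interim, about 0.048 would use the full 5%. Any such revision should be made before the interim data are seen.

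The cost is one corrected figure and one added sentence. The number of patients does not change.
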